#### **4.3 Subject Completion/ Withdrawal procedures**

Any clinic wishing to withdraw from the intervention group can do so at any time.

#### **4.4 Screen failure procedures**

Providers in the intervention clinics will continue to provide usual care to all patients that do not screen into the study.

### **5 SCREENING AND MONITORING EVALUATIONS AND MEASUREMENTS (how measurements will be made)**

In addition to the focus group instruments and web-based surveys, the development of which are detailed in Section 3, the following outcomes will be used for the cluster-randomized trial.

**The primary outcome for this study is opioid and BZD exposure, as measured by dose and discontinuation rate. A secondary outcome variable is the rate of falls.** We will also evaluate providers' satisfaction with the deprescribing toolkit. For clinicians providing services at an Intervention Group clinic, we will assess three outcome variables that reflect the process of service delivery: (1) whether or not their patients received education on opioids and BZD and their relationship to falls; (2) whether or not the deprescribing toolkit was utilized as part of the deprescribing process; and (3) whether or not HCPs referred to deprescribing toolkit recommendations concerning medication and non-medications to reduce the patient's risk of falls.

➤ **Opioid and BZD Exposure:** The primary outcome of this study will be exposure to opioid and/or BZD. This will be measured in two ways: (1) dose and (2) discontinuation. We will convert all opioid prescriptions to morphine milligram equivalents (MME), and all BZD prescriptions to diazepam milligram equivalents (DME). The method for calculating MME is well-established, and recommended by the CDC for evaluating opioid-related complications. Calculating DME is analogous, and has been used in previous work to evaluate exposure to BZD and has been used previously to evaluate success of discontinuation interventions. For each class of medications, we will calculate milligram equivalents for all observable prescriptions in the 12 months prior to the index and in the 12 months

post-index. To create a more conservative estimate of the impact of the intervention, we will assume that any authorized refills were filled. [DATA SOURCE: Epic EHR]

Discontinuation will be defined as a lack of opioid or BZD prescription from 181 to 360 days after the index. It is acknowledged that the intervention may not have an immediate impact on opioid and BZD discontinuation as prescribers taper patients' doses down, therefore a gap is given to allow for tapering in advance of discontinuation. [DATA SOURCE: Epic EHR]

➤ **Risk of Falls:** The secondary outcome of this study will be patients' falls risk, as identified by patients' recorded responses to the STEADI questions embedded in the EHR and by the rate of falls during the one-year post-intervention period compared to the one-year pre-period. We will obtain information regarding falls using data from Epic EHR, and research team members will record the number of injurious falls-related visits made during pre-intervention and post-intervention periods. [DATA SOURCE: Epic EHR]

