### 6.4.2 Discontinuation rate of opioids

According to a recent systematic review of literature, most opioid continuation rates are from relatively unreliable studies and can be anywhere between 54% to 100%. However, a recent study has found the odds ratio of opioid discontinuation in control versus treatment group to be 1.5 (95% CI [1.0-2.1]). If clinics are randomly assigned to a treatment group and a control group, with an equal number of patients in both groups, a GEE model (binary outcome) with a total sample size of 3000

patients, each measured two times before and after intervention, will have statistical power in the range of 0.631-0.953 to detect differences in odds ratios in the range of 1.30-2.0. There is significant drop in power for detecting differences in odds ratios below 1.3. Baseline probabilities in the treatment and control group are assumed to be in the range of 0.020-0.050 and we assumed a 20% attrition rate. For lower baseline probabilities of 0.010 in each group, the statistical power is in the range of 0.485-0.860 for detecting odds ratios of 1.3 or higher.

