## **6.7 Handling of Missing Values**

We will apply no imputation method to this data. All data are observational, and randomization should balance missingness across samples. As such, it is unlikely that missing values will create selection bias. Additionally, our chosen statistical method allows for estimation of longitudinal effects even if patients have a missing outcome value.

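### Discontinuation is scored from the absence of EHR prescriptions on days 181-360 without requiring that the patient is alive and still observed, and section 6.7 does not repair this

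*Protocol*

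**What the plan says.** Protocol section 5 makes opioid and BZD exposure the primary outcome, measured by dose and by discontinuation. The discontinuation rule reads: "Discontinuation will be defined as a lack of opioid or BZD prescription from 181 to 360 days after the index". The source is given as "DATA SOURCE: Epic EHR". Dose is totalled over the observable prescriptions in the 12 months before and the 12 months after index, and for that purpose "we will assume that any authorized refills were filled". No corresponding refill rule is stated for discontinuation.

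Section 4.2 collects data on all potentially eligible patients, and section 6.3 invokes intention to treat. Loss is expected: for opioid discontinuation in section 6.4.2, "we assumed a 20% attrition rate".

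On missing data, section 6.7 says "We will apply no imputation method to this data" and argues: "All data are observational, and randomization should balance missingness across samples. As such, it is unlikely that missing values will create selection bias". It adds that "our chosen statistical method allows for estimation of longitudinal effects even if patients have a missing outcome value". Section 8 says that missingness will be explored and that imbalance between arms will go to the study team, without an analysis rule. Section 3.3 excludes patients whose problem list shows cancer, cognitive impairment, hospice care or skilled-nursing residence. It does not mention death or departure.

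**The concern.** A prescription can be absent because the drug was stopped, or because the patient died, moved away or went to a prescriber outside the system. The rule cannot tell these apart. A patient with no records at all in days 181-360 meets it, so that patient is an event and not a missing value. The dose outcome has the same weakness: prescriptions that can no longer be observed add nothing to the post-index total.

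The section 6.7 argument misses this for three reasons.

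- Under the rule these patients have an outcome, so neither GEE's handling of missing outcomes nor the missingness review in section 8 would pick them up.
- Randomisation balances baseline characteristics in expectation, here across only 20 clinics. Loss comes later and may be affected by the intervention. Section 7 itself anticipates increased pain, anxiety and poor sleep from deprescribing, which are plausible reasons to look for another prescriber.
- Balance would not be enough. Adding the same share of false events to both arms draws the odds ratio toward 1.

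At stake is whether a positive or null result on a primary outcome can be attributed to deprescribing.

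**Working it through.** **Inputs from the protocol.** 3,000 patients, so 1,500 per arm under an equal split; 20 clinics, 10 per arm; 20% attrition, leaving 1,500 × 0.8 = 1,200 per arm; baseline probability 0.02-0.05 for opioid discontinuation (6.4.2); two-sided alpha 0.05.

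**Assumptions, not in the protocol.** Every lost patient is prescription-free for the whole of days 181-360. The true post-index control rate equals the stated baseline (5%). As a high alternative it is 27%, the lower end of the discontinuation range that 6.4.4 cites for BZD interventions. Loss is either equal at 20%, or 25% in the intervention arm v 20% in control.

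**The plan's own figures.** Section 6.4.2 states power of 0.631-0.953 for odds ratios of 1.30-2.0. A simple two-proportion test at 1,200 per arm gives 0.158 (baseline 2%) to 0.317 (5%) at 1.3, and 0.793 to 0.990 at 2.0. The stated range is therefore not reproduced without an unstated within-patient correlation, but nothing below depends on it. The lower bound in 6.4.3 (0.678) does reproduce. With difference 0.25, SD 2, correlation 0.2 and 1,200 per arm, SE = 2 × √(4 × 0.8 / 1,200) = 0.1033. Then 0.25/0.1033 − 1.96 = 0.46, and power is 0.677. With 1,500 per arm it would be 0.772. So that calculation takes lost patients out of the denominator, whereas the discontinuation rule keeps them in as events.

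**Effect of the rule.** With loss share a and true rate p, scored rate = a + (1 − a)p.

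| Control rate | Scenario | Scored intervention v control | Apparent OR |
|---|---|---|---|
| 5% | true OR 1.5 (7.32%), equal 20% loss | 0.2585 v 0.2400 | 1.10 |
| 5% | true OR 2.0 (9.52%), equal 20% loss | 0.2762 v 0.2400 | 1.21 |
| 5% | no effect, 25% v 20% loss | 0.2875 v 0.2400 | 1.28 |
| 27% | true OR 1.5 (35.68%), equal 20% loss | 0.4855 v 0.4160 | 1.32 |
| 27% | true OR 2.0 (42.52%), equal 20% loss | 0.5402 v 0.4160 | 1.65 |
| 27% | no effect, 25% v 20% loss | 0.4525 v 0.4160 | 1.16 |

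For the third row: (0.2875/0.7125) / (0.24/0.76) = 0.4035/0.3158 = 1.28. Reversing the imbalance gives 0.3158/0.4035 = 0.78, so the direction is not fixed.

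**Share of control events that are losses** under equal 20% loss: 0.20/0.24 = 83% at a 5% rate; 0.20/0.416 = 48% at 27%.

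**Power** for a true OR of 1.5 at a 5% control rate, ignoring clustering: 0.656 with losses removed (1,200 per arm), 0.216 with losses scored as events (1,500 per arm).

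**Opposite coding.** If lost patients count as not discontinued, scored rate = (1 − a)p. With no effect, a 5% rate and 25% v 20% loss, this is 0.0375 v 0.0400, and the OR is (0.0375/0.9625)/(0.04/0.96) = 0.94. The two codings bracket the true value of 1 in this example.

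**The case against.** The strongest reply is that the planners meant lost patients to be missing. Section 6.7 speaks of patients with a missing outcome, the power section allows for attrition, and 6.4.3 reproduces only with the lost removed. Observability rules are often left to a statistical analysis plan, and none is shown here. That may well be the intention, but the protocol itself fixes the outcome rule, and the rule never yields a missing value for someone who has left. If lost patients were in fact set to missing, the misclassification arithmetic would fall away, and what remained would be the weak argument that randomisation balances post-randomisation loss.

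The size is also open to challenge, and this stands. Someone who leaves on day 250 may have a prescription in the window. The 2-5% is a baseline probability in a pre-post model and not clearly the post-index rate. The protocol gives no loss rates by arm. At higher control rates the distortion shrinks.

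Sections 3.3 and 8 give partial cover: facility or hospice entry may be caught if the problem list is read after baseline, and imbalance in recorded missingness would be reported. Neither reaches death or departure coded as an event.

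A reader might infer four stronger claims that the protocol does not support:

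- That section 6.7 says randomisation removes bias from death and departure. It says only that missingness should balance and that bias is unlikely, and it names neither event.
- That lost patients would necessarily supply most events. That depends on the low assumed rate.
- That GEE is valid only when data are missing completely at random. Missingness explained by modelled covariates can also be tolerated, and the more basic point is that these patients are not missing.
- That the refill rule contradicts the discontinuation rule. A prescription whose refills run past day 180 can be read as present, so the text is ambiguous, not contradictory.

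**Conclusion.** The point holds as a defect in the outcome rule and in the reasoning of section 6.7. Followed as written, the rule turns loss from the system into discontinuation and understates post-index dose. The odds ratio is diluted when loss is equal and biased in either direction when it is not.

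The illustrated distortion is a true OR of 1.5 appearing as 1.10 (5% control rate) to about 1.32 (27%), and a null effect appearing as 1.28 to about 1.16 under a 25% v 20% loss. Only the 20% attrition and the 5% baseline are the protocol's. The loss split, the 27% control rate, the use of the baseline as the post-index rate, and full absence of prescriptions among the lost are assumptions. The effect on dose was not quantified. The need for correction rests on the wording and not on any one of these figures.

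**What to change.** **Section 5.** State that patients who die, or for whom there is no evidence of remaining in the system during days 181-360, are treated as unobserved and not scored as discontinued. Report death and departure by arm. Say what counts as evidence: a single encounter at any time after day 181 does not show observation through day 360. Apply observed follow-up time to the dose outcome in the same way. State that a prescription whose authorised refills run into days 181-360 counts as present, consistent with the dose rule.

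**Section 6.7.** Replace the claim that randomisation makes selection bias unlikely with an analysis weighted by the inverse of the probability of being observed, estimated from baseline EHR data. Add an intention-to-treat sensitivity analysis that keeps all patients and counts lost patients as not discontinued.

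**Cost.** The change is wording plus programming on EHR data, with fewer evaluable patients. The observability condition is itself post-randomisation, and weighting corrects only for loss explained by recorded baseline factors. For that reason the weighted and all-patient analyses are both needed.

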The literature shows progression over time in our awareness of the role of medications in falls and an increasing sophistication of interventions, including successful interventions in pharmacies. Policy makers and payers are starting to support these efforts. The Centers for Medicare and Medicaid Services regulations including Medicare Part D now require medication reduction strategies and numerous quality improvement projects focus on reducing high-risk medications to prevent falls.

**Engaging the Entire Health Care Management Team in Falls Prevention for Older Adults.** The American Geriatrics Society/British Geriatrics Society Clinical Practice Guideline for Prevention of Falls in Older Persons recommends that healthcare providers (HCPs) ask all older adults about falls, their frequency of falling, and difficulties in gait or balance on an annual basis. However, this screening occurs infrequently in clinical practice. For example, in one study, only 25% of older adult patients reported they had been asked about falls annually and only 48% reported they had ever been asked about falls. Another study, based on a nationally-representative sample of Medicare beneficiaries, found that less than 30% of the individuals who had experienced a fall within the previous year had received counseling about fall prevention from their health care provider. We could only find one study that engaged the entire health care team in reducing the risk of falls. Engaging the entire health care team may help patients adopt and maintain behaviors that reduce falls risk especially as it relates to opioid and BZD deprescribing. Regarding deprescribing, only a few studies focus on a patient centered approach including education and cognitive behavioral therapy in addition to deprescribing. This study will use a team-based approach to screen patients and de-prescribe opioids and BZDs for patients at risk for falls in the outpatient setting.

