### **4.2 Screening/Baseline Visit Procedures and Observation Procedures for the Cluster-Randomized Trial:**

- (1) Randomize intervention and control clinics:** A list of clinics that are interested in participating will be compiled by the primary investigators. A member of the study team, [name], PhD, will use the random number generator built into SAS to randomize 10 clinics into treatment and 10 clinics into control groups. If the number of potentially eligible clinics exceeds 20, 20 clinics will be chosen at random, and this list will subsequently be divided into 10 random treatment clinics and 10 random controls. Results of randomization will be provided to the study coordinators, who will inform clinics of their status.

Data for all patients who meet inclusion criteria will be included in this analysis. This educational

intervention is intended to better inform providers in intervention clinics as to the fall-related risks associated with opioids and BZDs as well as best practices in deprescribing opioids and BZDs. A toolkit to support screening and deprescribing will also be provided to providers at intervention clinics. It is expected that providers will use this information to attempt deprescribing for any patients for whom they feel the benefits of deprescribing outweigh the risks. The study team will collect data from the EHR on all potentially eligible patients, regardless of any attempted deprescribing. The same data will be collected for patients who received care from treatment and control clinics.

**(2) Screen for risk of falling:** Intervention group clinics will be expected to screen all patients who appear on the baseline report for falls risk, questions if the patient has not already been screened previously, by using the STEADI screening questions. Each clinic will be allowed to determine how they will integrate these questions into the patient care process. Although the processes used to integrate the screening questions into patient care will vary across clinics, all clinics will be required to enter patient responses to the questions into the EHR, as is standard practice in all UNC HealthCare clinics.

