**Secondary Analyses:** Our secondary hypothesis is:

- Relative to individuals in both control groups, individuals in both intervention groups will experience a reduction in the risk of experiencing a fall following the index date.

Risk is operationalized as the odds of experiencing a fall in the 12-month post-index compared to the 12 months pre-index. The models used for this analysis match those in Equation 1, with the exception that the models for fall risk will use a log link with a binomial distribution instead of an identity link with a normal distribution.

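### The falls outcome draws partly on STEADI answers that only intervention clinics are told to collect from all listed patients, and its stated odds do not match the log-link model

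*Protocol*

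**What the plan says.** Protocol Section 5 (Risk of Falls) names two sources for the secondary outcome, joined by *and*: patients' "recorded responses to the STEADI questions embedded in the EHR and by the rate of falls during the one-year post-intervention period", compared with the year before. It adds that "research team members will record the number of injurious falls-related visits made during pre-intervention and post-intervention periods".

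Section 4.2, step (2), sets the screening duty: "Intervention group clinics will be expected to screen all patients who appear on the baseline report for falls risk", with the qualifier "if the patient has not already been screened previously". Step (6) trains intervention-clinic staff to ask these questions of the older adults on the baseline report. No section gives control clinics the same duty or training. Step (2) does describe entering the answers in the record as standard practice across the health system.

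Section 6.3 (Secondary Analyses) states the effect measure and the model: "Risk is operationalized as the odds of experiencing a fall in the 12-month post-index compared to the 12 months pre-index", and "the models for fall risk will use a log link with a binomial distribution". Section 6.2 and the opening of Section 5 call the same outcome a rate.

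**The concern.** There are two separate problems.

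The first is ascertainment. An outcome source that the intervention itself prompts staff to fill in can be more complete in that arm whatever happens to actual falls. Section 6.3 sets the intervention index date at the first intervention-related clinical activity, so the extra recording would fall at or after index. It would then enter the arm-by-period coefficient, β3, which is the effect estimate. The direction is unfavourable to the programme: more recorded falls in the intervention arm could hide a real benefit or make it look like harm. Section 6.7 expects randomization to balance missingness, but randomization cannot balance a recording difference that the assigned intervention creates.

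The second is the effect measure. Odds, risk and rate are different quantities, and the protocol attaches all three to one endpoint. A reader of the results would not know which ratio is being reported.

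**Working it through.** The protocol gives no sample size, power or effect figure for falls (Sections 6.4.1 to 6.4.4 cover only dose and discontinuation), so there is no stated figure to reproduce. Two checks follow.

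**Ascertainment.** Inputs:
- *p*, annual fall risk: 0.25, from the one-in-four figure in Section 1.3. It is taken as equal in both arms (no true effect).
- *s*, share of patients screened in the post period: not given for either arm. For the intervention arm I assume 1.00, as the instruction intends. For control I use a range that includes two background figures from Section 1.3: "only 25% of older adult patients reported they had been asked about falls annually", and 48% ever asked. These come from a cited study, not from this health system.
- *v*, share of falls seen as a visit whatever the screening: not given. Assumed to be 0, 0.5 or 1.
- Pre-period capture: assumed equal in both arms, so the ratio of risk ratios equals the post-period ratio.

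Recorded risk = *p* × [*v* + (1 − *v*) × *s*]. With full intervention screening this is 0.25 for every *v*. The spurious ratio is therefore 1 / [*v* + (1 − *v*) × *s*(control)], and *p* cancels.

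| Control screening | *v* = 0: control risk, ratio | *v* = 0.5: control risk, ratio | *v* = 1: ratio |
|---|---|---|---|
| 25% | 0.0625, 4.0 | 0.156, 1.60 | 1.00 |
| 48% | 0.120, 2.08 | 0.185, 1.35 | 1.00 |
| 80% | 0.200, 1.25 | 0.225, 1.11 | 1.00 |
| 100% | 0.250, 1.00 | 0.250, 1.00 | 1.00 |

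Example for 48% and *v* = 0.5: 0.25 × (0.5 + 0.5 × 0.48) = 0.185, and 0.25 / 0.185 = 1.35.

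With a true risk ratio of 0.80 and 48% control screening, the intervention risk is 0.20. The observed ratio is 0.20 / 0.12 = 1.67 at *v* = 0 and 0.20 / 0.185 = 1.08 at *v* = 0.5.

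**Effect measure.** Under a log link, exp(β3) is a ratio of risk ratios. A ratio of odds ratios needs a logit link. Take control risk as constant and convert with odds = risk / (1 − risk):
- Pre-period risk 0.25, risk ratio 0.80: post risk 0.20; odds 0.20/0.80 = 0.250 against 0.25/0.75 = 0.333; odds ratio 0.75.
- Pre-period risk 0.25, risk ratio 0.70: odds 0.175/0.825 = 0.212; odds ratio 0.64.
- Pre-period risk 0.05, risk ratio 0.80: odds 0.04/0.96 = 0.0417 against 0.05/0.95 = 0.0526; odds ratio 0.79.

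The rate wording adds a third quantity. A patient with three injurious-fall visits contributes three events to a count but only one to a yes/no fall.

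**The case against.** The best defence is that the modelled fall may never use STEADI. Section 5 goes on to describe a count of injurious-fall visits, its opening and Section 6.2 name only the rate of falls, and Section 6.3 models the experience of a fall without naming STEADI. If only visits count and both arms record them equally, the spurious ratio is 1.00. This stands as a limit on the claim. It does not dispose of it, because Section 5 puts STEADI responses in the outcome definition and Section 6.3 does not say which source supplies the modelled variable. If STEADI is a separate component, it is still open to unequal recording by arm.

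A reader might infer that screening happens in one arm only. The protocol does not support that: already-screened patients are exempt and entry of answers is called routine in all clinics. Only the added instruction and training are arm-specific. Routine entry, however, is not a screening rate. Section 4.2 also says the same data are collected in both arms, but that equalises extraction, not the asking of the questions.

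A reader might also combine the one-in-four figure, the 25% asked, and the 70% screened in Section 1.1 into a false ratio of 2.8 (0.25 × 0.70 = 0.175; 0.25 × 0.25 = 0.0625). That should not be taken as the expected size. The 25% is patient recall in another study, the 70% comes from a community-pharmacy programme, and the sum assumes that no fall is ever seen as a visit.

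Finally, the protocol does not say whether staff who record visits are masked to arm. Silence on this is not a defect, since such detail can sit elsewhere.

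On the link, the defence is that the hypothesis concerns risk, so the model fits it and only the word *odds* is wrong. That is fair: the mismatch does not bias the test, and the gap is small for rare events.

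**Conclusion.** Both points hold, within limits.

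The outcome definition includes a source that only intervention clinics are told and trained to complete for all listed patients not yet screened. STEADI-based falls may therefore be recorded more fully in that arm after index, which would bias β3 against the intervention. That more falls *will* be found there is not established. The possible size runs from none (ratio 1.00) to 4.0, depending on control screening and on how many falls are also seen as visits, and the protocol gives neither. The range also assumes full intervention screening and equal capture before index.

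The effect-measure contradiction is certain and needs no assumption: a binomial model with a log link does not estimate the stated odds, and the outcome is elsewhere called a rate. Its consequence is mislabelling (0.80 against 0.75 at 25% risk), not a biased test.

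The outcome is secondary, but reducing falls is the declared purpose of the programme, and both repairs are cheap. They should be made.

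**What to change.** - In Sections 5 and 6.3, define the falls endpoint only from injurious-fall encounters in the electronic record, found by one code list applied identically in both arms. Emergency department and inpatient encounters are preferable, because coding at the trained clinics' own visits may also be changed by the intervention.
- Remove STEADI responses from the outcome. Report them as a process measure, with the proportion screened in each arm.
- In Section 6.3, replace odds with risk and report a risk ratio under the log link. If an odds ratio is wanted, use a logit link instead.
- Bring the rate wording in Sections 5 and 6.2 into line, and likewise where Sections 2 and 2.2 use the same term.

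The cost is a few sentences and a code list. The screening itself need not change. The drawback is that non-injurious falls, and falls seen only in clinic, would not be counted.
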